#### Incremental cost-effectiveness

A probabilistic decision analytic Markov model developed for our recent telephone-delivered lifestyle intervention trial will be adapted and used to evaluate incremental cost-effectiveness [42]. The structure, data requirements, methods for calibration and model evaluation are described in a recent methodological peer reviewed publication [91]. The model describes the health states relevant to intervening on weight loss, physical activity, and glycaemic control in adults with type 2 diabetes. A societal perspective is adopted and values collected for variables that describe the participant's use of acute and primary care health services, their private out of pocket expenditures and the time costs to informal carers. Patient-based production losses are not included on the cost side of the analysis but (implicitly) counted within the QALY estimation in line with current theory and recommendations [92]. The model implies the trial participants face some probability of remaining in a sub-optimal health state or transitioning to improved health states (i.e. improvements in weight, physical activity and glycaemic control) and there will be a small chance of transitioning to death. Cycle duration is based on the timing of data collection for health-related quality of life (i.e. baseline, 6, 18, and 24 months). The transition probabilities that reflect consistency with study intervention targets surrounding primary outcomes (i.e., 5% weight loss, 210 min/wk moderate-to-vigorous PA, < 7% HbA1c) will be used to predict movement through the states for all cycles; this approach is shown in a previous economic analysis [42]. Costs and utility based preference scores will be estimated for each cycle and summarised to estimate change in costs and change in QALYs. The relevant ICER will be estimated and cost-effectiveness acceptability curves plotted to illustrate the probability that the intervention is cost-effective [109].

#### Moderators and mediators of outcome

Exploratory analyses will be conducted to determine whether there is moderation or mediation of intervention effects using previously established methods [95,96]. Moderator analysis will determine whether intervention effects differ across demographic (e.g. age, gender) and medical (e.g. insulin use) characteristics and will be performed by considering the statistical significance of an interaction between a potential moderator and the intervention using a Wald test.

Mediator analysis will determine whether theoretically-driven constructs and mechanisms for behaviour change do in fact mediate the intervention effects. Potential mediators will be assessed using path analysis. Point estimates and bootstrap confidence intervals of path coefficients and the product of the mediated path coefficients will be used to determine the potency, certainty and direction of any mediation effect [110].

### Sample size

Effect size estimates for the proposed study take into account clinically meaningful differences and are based on published results [24,111,112], and unpublished data from our recent trials. The minimum differences of interest in change from baseline to 18-months follow-up between intervention and usual care groups for our primary outcomes are: -5% of initial body weight; +60 minutes/week for moderate physical activity; -0.6% for HbA1c. Sample size estimates are based on the expected mean difference for physical activity, as this variable required the largest sample size. To detect a mean difference of 60 minutes per week change in accelerometer-derived moderate-to-vigorous intensity physical activity between the intervention and control groups with 90% power and 5% significance (two-tailed), assuming a standard deviation of 140 minutes (based on unpublished data), requires 115 subjects per group. Assuming an attrition rate of 30% means that 150 participants per group are required (300 participants overall). This sample size provides sufficient power (80% or more) to detect the following intervention effects for sedentary time (-45 minutes/day); light intensity time (+30 minutes/day); and, our secondary outcomes: -2,000 kJ for energy intake; -5% for energy from fat; -2% for energy from saturated fat; -5 to 10% for cholesterol (total, LDL-, HDL-); -15% for triglycerides; -1 mmol/L for fasting plasma glucose; -5 mmHg for systolic blood pressure; -5 cm for waist circumference; and, -2% for body fat.

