### Practice sampling and recruitment

General practices are recruited from the Southeast Primary Health Care Network (SPHN), a state and federally funded organization that provides administrative, technical and professional development/educational support to local area practices. At study commencement, SPHN supported 76 practices. The study will recruit 10 practices over two years, with approximately 30 adults enrolled from each practice. To ensure an adequate patient sampling frame from each practice, practices are ranked in order of descending number of GPs, with the largest practices approached first on a rolling basis until 10 practices (or the required sample size of 300 participants) consent to participate. Practices are initially contacted by telephone to determine whether electronic medical records can be used to perform patient searches by medical condition, and whether approximately 200 patients with type 2 diabetes can be identified. Eligible practices are sent an invitation letter and study brochure. This is followed-up by a phone call from a GP working within the SPHN (author KW), and a practice visit from the project manager to solicit consent.

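### Sample size: 150 per group with 30% attrition leaves 105, not the 115 per group said to be needed, so 300 participants give about 87% power rather than 90%

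*Protocol article*

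**What the plan says.** The Sample size section bases the calculation on accelerometer-measured moderate-to-vigorous physical activity, because that primary outcome needed the most participants. The target is given as "To detect a mean difference of 60 minutes per week change in accelerometer-derived moderate-to-vigorous intensity physical activity" between the groups, "with 90% power and 5% significance (two-tailed"), and the section continues: "assuming a standard deviation of 140 minutes (based on unpublished data), requires 115 subjects per group". The minimum differences of interest are defined on change from baseline to 18 months.

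The next sentence makes the allowance for loss: "Assuming an attrition rate of 30% means that 150 participants per group are required (300 participants overall"). No formula or other basis is given for going from 115 to 150.

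The total of 300 also appears in the Abstract. In Practice sampling and recruitment, "the required sample size of 300 participants" is one of the two points at which the approach to further practices stops.

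**The concern.** An attrition rate is the share of randomised participants who are lost. If 30% are lost, the number to randomise is the evaluable number divided by 0.70. Multiplying by 1.30 gives too few, and 150 is what multiplication gives. On the plan's own inputs, the trial would then finish with fewer evaluable participants than it says it requires.

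What is at stake is the accuracy of the power claim for the outcome that fixes the trial's size. A reader who takes the section at face value would believe that the trial keeps 90% power for 60 min/week after losing 30% of its participants. The same total also governs when practice recruitment stops, so the figure affects conduct as well as reporting.

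**Working it through.** **Inputs, all from the Sample size section**

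- Difference in change: 60 min/week
- SD: 140 min/week
- Two-sided 5% level (z = 1.960) and 90% power (z = 1.2816)
- Evaluable number stated: 115 per group
- Attrition stated: 30%
- Number to randomise stated: 150 per group, 300 overall

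**Step 1. Reproduce the evaluable number.**

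n per group = 2 × (1.960 + 1.2816)² × 140² / 60² = 114.4, rounded up to 115. This matches the plan. A t-test calculation gives 115.4, so 116, which is the same for practical purposes.

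**Step 2. Reproduce the number to randomise.**

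- Multiplying: 115 × (1 + 0.30) = 149.5, so 150. This matches the stated figure.
- Dividing: 115 / (1 − 0.30) = 164.3, so 165 per group, 330 overall. This does not match, and rounding cannot close a gap of 15 per group.

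**Step 3. What 150 per group leaves.**

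150 × 0.70 = 105 per group, 210 overall. That is 10 per group below 115.

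**Step 4. Power at that number.**

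Standard error = 140 × √(2/105) = 19.32. Then 60 / 19.32 = 3.105, and 3.105 − 1.960 = 1.145. Φ(1.145) = 0.874.

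| Evaluable per group | How it arises | Power, normal | Power, t-test |
|---|---|---|---|
| 105 | 150 randomised, 30% lost | 87.4% | 87.1% |
| 115 | the stated requirement | 90.1% | 89.9% |
| 115.5 | 165 randomised, 30% lost | 90.3% | 90.0% |
| 150 | 150 randomised, none lost | 96.0% | 95.9% |

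**Step 5. The same shortfall on two other scales.**

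- Difference detectable with 90% power at 105 per group: (1.960 + 1.2816) × 19.32 = 62.6, about 63 min/week instead of 60.
- Largest attrition at which 150 per group still leaves 115: 1 − 115/150 = 23.3%.

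**The case against.** There are four points on the other side.

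*The planned analysis may be more precise than the calculation.* The Statistical analyses section specifies a mixed model with baseline values as a covariate and analyses participants whatever follow-up they miss. Physical activity is also measured at 6 and 12 months, so people lost before 18 months can still contribute. Regaining 90% power with 105 per group needs the variance to fall to 105/114.4 = 0.918 of the assumed value. If 140 is the SD of change and the variance is equal over time, baseline adjustment multiplies the variance by (1 + ρ)/2, where ρ is the correlation between baseline and 18 months. That suffices for any ρ below about 0.83. If 140 is the SD at follow-up, the factor is 1 − ρ², which suffices for ρ above about 0.29. These are assumptions: the article gives no ρ and does not say which SD it means. The point stands to this extent: the 87% describes an unadjusted comparison, and the planned model could well do better. It does not rescue the stated sentence, because the sample size calculation neither invokes the model nor quantifies any gain from it.

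*Attrition might mean a mark-up on completers.* Read that way, 30% is a true loss of 35/150 = 23.3%. The text calls it an attrition rate and nothing in the article defines it otherwise.

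*The cause is inferred.* This is fair. The article shows no formula. Multiplication by 1.3 fits exactly, but the mismatch between 115, 30% and 150 stands however it arose.

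*The effect is small.* This is also fair. Power stays well above 80%, the level that the same section treats as sufficient for other outcomes.

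**Conclusion.** The concern holds. On the plan's own inputs, 90% power, 30% attrition and 150 per group cannot all be true. With 30% lost, power for 60 min/week is about 87% (87.4% normal, 87.1% t-test), a shortfall of 2.6 to 2.9 percentage points.

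This rests on the stated SD, on reading attrition as the share of randomised participants lost, and on the simple two-group comparison that reproduces the 115. It is an internal inconsistency in the justification of the sample size. It does not show that the mixed-model analysis will fall below 90%. The type I error rate, the outcomes and the analysis are unaffected.

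The section also claims at least 80% power for a list of other outcomes. It does not give their SDs or say how many evaluable participants were assumed, so nothing here shows that any of those claims fails.

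**What to change.** Keep 300 participants and correct the sentence in one of two ways:

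- *With 150 randomised per group and 30% attrition (105 evaluable per group), an unadjusted comparison has 87% power to detect 60 min/week.*
- *With 150 randomised per group, the trial has 90% power to detect 60 min/week provided attrition is no more than 23%.*

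If the team wants to rely on the gain from baseline adjustment, it should state the assumed correlation, say whether 140 is the SD of change or of the follow-up value, and give the resulting power.

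As a check, confirm that the claims of at least 80% power for the other outcomes hold at 105 per group, and state the number used.

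The cost is one sentence and a slightly less favourable stated power, with no additional participants. The alternative that meets every stated assumption is 165 per group, 330 overall. It costs 30 more participants and would require the total to be changed in the Abstract and in Practice sampling and recruitment.

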## Discussion

The epidemic of type 2 diabetes shows no signs of abating. Both weight loss and physical activity are independently associated with improved glycaemic control, lipids and blood pressure in type 2 diabetes [49] and are important diabetes management goals. Thus there is a need to develop, evaluate and disseminate approaches that are effective in promoting the maintenance of weight loss and physical activity. Telephone-delivered interventions show promise in this regard as they facilitate, in a cost-effective manner, [42] the repeated contacts and support necessary to promote maintenance.

The Living Well with Diabetes study is evaluating a broad reach strategy (telephone counselling), with emphasis on behavioural and physiologic outcomes, fidelity of implementation, incremental cost-effectiveness, and assessment of maintenance. These issues are important to advancing the science of mass reach approaches to weight management and health behaviour change, as well as building the evidence base for the translation of this work into population health practice.
